## Abstract

**Background:**

Chronic fatigue syndrome (CFS) is a debilitating multisystem disorder that can lead to various pathophysiological abnormalities and symptoms, including insomnia, gastrointestinal disorders, and anxiety. Due to the side effects of currently available drugs, there is a growing need for safe and effective nondrug therapies. The Prolong Life With Nine Turn (PLWNT) Qigong method is a system of mind-body exercise with restorative benefits that can alleviate the clinical symptoms of CFS and impart a significant inhibitory effect. Various studies have proven the treatment efficacy of PLWNT; however, the impact on insomnia, gastrointestinal disorders, and anxiety in patients with CFS has not yet been investigated.

**Objective:**

This study aims to evaluate the efficacy and safety of the PLWNT method in terms of its effects on fatigue, insomnia, anxiety, and gastrointestinal symptoms in patients with CFS.

**Methods:**

We will conduct a randomized, analyst-blinded, parallel-controlled trial with a 12-week intervention and 8-week follow-up. A total of 208 patients of age 20-60 years will be recruited. The patients will be randomly divided into a PLWNT Qigong exercise group (PLWNT Group) and a control group treated with cognitive behavioral therapy at a ratio of 1:1. Participants from the treatment groups will be taught by a highly qualified professor at the Shanghai University of Traditional Chinese Medicine once a week and will be supervised via web during the remaining 6 days at home, over 12 consecutive weeks. The primary outcome will be the Multidimensional Fatigue Inventory 20, while the secondary outcomes include the Pittsburgh Sleep Quality Index, Gastrointestinal Symptom Rating Scale, Hospital Anxiety and Depression Scale, functional magnetic resonance imaging, gut microbiota, and peripheral blood.

**Results:**

The study was approved by the ethics committee of Shanghai Municipal Hospital of Traditional Chinese Medicine in March 2022 (Ethics Approval Number 2022SHL-KY-05). Recruitment started in July 2022. The intervention is scheduled to be completed in December 2024, and data collection will be completed by the end of January 2025. Over the 3-year recruitment period, 208 participants will be recruited. Data management is still in progress; therefore, data analysis has yet to be performed.

**Conclusions:**

This randomized trial will evaluate the effectiveness of the PLWNT method in relieving fatigue, insomnia, anxiety, and gastrointestinal symptoms in patients with CFS. If proven effective, it will provide a promising alternative intervention for patients with CFS.

**Trial Registration:**

China Clinical Trials Registry ChiCTR2200061229; https://www.chictr.org.cn/showproj.html?proj=162803

**International Registered Report Identifier (IRRID):**

PRR1-10.2196/53347

## Introduction

Chronic fatigue syndrome (CFS) is a complex neuroimmune disease, usually characterized by severe fatigue, cognitive and autonomic dysfunction, and gastrointestinal discomfort, which seriously affect activities of daily living [1]. Mental sickness, sleep disorders, and gastrointestinal dysfunction are common symptoms reported by patients with CFS [2]. It is estimated that the average prevalence of adult CFS worldwide is approximately 0.65%, which rises to 0.89% if the most commonly used case definition is used [3]. Among patients with CFS, 82%-95% of people experience lifelong symptoms of mental and sleep disorders [4] and have a high need for health care [5]. In the general population in the United States and the United Kingdom, the prevalence of CFS ranges from 0.4% to 2.5% [6,7]. In 2015, the prevalence of CFS in the US population was approximately 836,000 to 2.5 million, among whom 42.2% and 33.3% of patients with CFS presented with anxiety and depression, respectively, according to data from the Institute of Medicine [8,9]. CFS has a greater negative impact on the patient’s physical and mental health.

In addition to neurological disorders, common symptoms reported by patients with CFS are characteristic of gastrointestinal diseases and are often accompanied by gastrointestinal symptoms such as nausea and vomiting [10,11]. Investigation into drug use in patients with CFS revealed that the use of antacids, H2 blockers, and proton pump inhibitors for the intestinal discomfort associated with CFS has increased significantly [12]. From a medical perspective, CFS is clinically regarded as part of a series of disease symptoms, including fibromyalgia and irritable bowel syndrome, and it may be related to the influence of the gastrointestinal digestive system or autoimmune symptoms [13]. Further evaluation of the role of intestinal flora in CFS neurological symptoms expression has suggested higher levels of D-lactic acid–producing enterococci and streptococci in the intestinal flora of patients with CFS compared with healthy controls [14]. The acute manifestations of D-lactic acidosis overlap with the psychiatric symptoms of CFS, prompting the use of drugs that target the commensal enteric microbiota as a possible treatment for the neurological symptoms of CFS [15]. Increasing evidence shows that CFS gastrointestinal symptoms may be related to various other symptoms, including, but not limited to, neurological symptoms. Thus, microbial imbalances should not be viewed in isolation [14]. Previous studies have indicated that nerve and gastrointestinal symptoms of CFS may be caused by food, such as dairy products and alcohol [16,17]. Neurological and gastrointestinal symptoms decrease during fasting, which is shown to be related to disruption of the brain-gut interaction [18]. It has also been reported that the traditional Chinese medicine Tianma, which is often used to treat headaches, not only relieves CFS but also regulates the intestinal flora [19]. This suggests that the brain-gut interaction plays a key role in CFS. The gut-brain interaction occurs through a variety of two-way pathways, including the central and enteric nervous systems or neuroimmune pathways and intestinal microbiota [20,21].

Both drug and nondrug therapies have been used for the prevention and treatment of CFS. Symptomatic treatment is often used in clinical treatment, including nonsteroidal anti-inflammatory drugs, exercise therapy, and cognitive behavioral therapy (CBT), which can relieve gastrointestinal and mental symptoms and improve the quality of life. The latest CFS treatment guidelines emphasize the change in the overall treatment attitude of CFS; for instance, drug treatment is now regarded as an adjuvant treatment of CFS nonpharmacological intervention [22]. Several researchers have proposed that graded exercise therapy and CBT might be effective treatments for CFS to improve fatigue and poor mental health, including depression, anxiety, and schizophrenia [23,24]. However, evidence of persistent and sustained substantial outcomes in patients with CFS is insufficient [25]. The clinical manual published by the International Association of Chronic Fatigue Syndrome recommends traditional Chinese medicine treatments, including acupuncture, massage, and Qigong. Qigong, as an intervention with proven safety and efficacy, has been recommended for the control of gastrointestinal diseases according to the clinical practice guidelines developed by the expert working group of the Sociedad Espanola de Patologia Digestive [26,27].

As one of the traditional Qigong (pronounced “chee gun”) for optimizing and restoring physical and mental energy, the prolong life with nine turn (PLWNT) method has a history of thousands of years, which was circulated by a centenarian named Kai Fang in the Qing Dynasty [28]. The PLWNT method, which can be practiced either statically (sitting, lying, and standing) or dynamically (moving), includes 8 kinds of massage manipulations on the abdomen and a kind of upper body shaking [29]. The abdominal massage techniques act on the movement of the pelvic and abdominal muscles, coordinated with diaphragmatic breathing. This may trigger the contraction of the intestinal and rectal muscles [30], which can train the function of the intestines [31] and impact the nervous system by reducing the excitability of the sympathetic nerve and enhancing the excitability of the parasympathetic nerve to reduce anxiety when rubbing the internal organs [32,33]. Long-term practice of PLWNT helps relieve the disease and regulate the functional activities of the meridians and viscera [34,35]. Moreover, exercisers can achieve “relaxation of mind and body” and “unity of nature and man,” thereby experiencing emotional stability and enhancing physical strength and health [36-38]. In our previous studies [39], it was confirmed that PLWNT is effective in reducing fatigue and improving the quality of life; however, whether the PLWNT has gastrointestinal, sleep, and emotional effects and the mechanism underlying these effects remains unclear.

In recent years, the brain-gut axis has been found to play an increasing role in the pathogenesis of CFS. The dysfunction of the central nervous system in processing gastrointestinal signals is considered to be a cause of CFS [40,41]. Moreover, previous studies have shown obvious abnormalities in the brain function activities and the species diversity of the gut microbiota in patients with CFS [42,43]. However, there has been no previous report on the use of PLWNT Qigong therapy to prove whether it can alleviate the clinical symptoms and regulate brain-gut interaction in patients with CFS. Therefore, we plan to use functional magnetic resonance imaging (fMRI) to analyze brain activity and connectivity data and collect stool samples to analyze the composition of the intestinal microbiota in patients with CFS.

This randomized controlled trial will be conducted based on the hypothesis that the application of PLWNT could alleviate fatigue, insomnia, anxiety, and gastrointestinal symptoms in patients with CFS. The study objectives are as follows: (1) to verify that PLWNT has a positive effect on fatigue, insomnia, anxiety, and gastrointestinal symptoms in patients with CFS compared with CBT, and (2) to fully explore the mechanism underlying the brain-gut regulation in CFS.

## Methods

### Study Design

A total of 208 patients with CFS who meet the requirements will be randomly assigned to the PLWNT group and CBT group. The PLWNT group will be treated with Qigong, and the control group will be treated with CBT (Figure 1). Patients will focus on offline practice once a week and via web practice at home 6 times a week for 12 weeks. The study protocol was developed in accordance with the SPIRIT (Standard Protocol Items: Recommendations for Intervention Trials) [44].

**Figure 1 figure1:**
[figure not shown]
Flow diagram of the study design. CBT: cognitive behavioral therapy; fMRI: functional magnetic resonance imaging; GSRS: Gastrointestinal Symptom Rating Scale; HADS: Hospital Anxiety and Depression Scale; MFI-20: Multidimensional Fatigue Inventory 20; PLWNT: prolong life with nine turn; PSQI: Pittsburgh Sleep Quality Index.

### Participant Recruitment and Informed Consent

A total of 208 participants will be recruited via WeChat (Tencent co, Ltd) or posters positioned at the Shanghai Municipal Hospital of Traditional Chinese Medicine from July 2022 to December 2024 in Shanghai, China. We will also include hospitalized patients with a preliminary diagnosis of CFS, according to the latest guidelines for the treatment of CFS revised in 2021 [45]. Before the commencement of the study, information on the study protocol will be provided to each participant. Participants will be briefed on the study process and informed of their responsibilities, and they will be informed that participation is entirely voluntary and that they may withdraw at any time. Once a participant has withdrawn, the collected data will not be deleted and will be used in the final analyses. Written informed consent will also be obtained from participants for this study, and the research assistant will be responsible for obtaining informed consent from all participants.

### Eligibility Criteria

#### Diagnostic Criteria

According to the latest NICE guidelines for 2021 [46], participants diagnosed with CFS must meet the criteria of debilitating fatigue worsened by activity, postexertional malaise, cognitive difficulties, and unresolved fatigue on awakening from sleep. All 4 symptoms must be present and have lasted for at least 3 months.

#### Inclusion Criteria

The study inclusion criteria are as follows: (1) age between 20 and 60 years; male or female; (2) severe chronic fatigue lasting at least 3 months, unexplained after clinical evaluation, not caused by work performed during the trial, and unable to be alleviated after rest; (3) meet the criteria of debilitating fatigue worsened by activity, postexertional malaise, cognitive difficulties, and unresolved fatigue upon awakening from sleep; (4) normal blood, urine, liver, and kidney functions; and (5) participants were not taking any other medication for 1 month prior to enrollment in this study and were not on any other treatment regimen.

#### Exclusion Criteria

The exclusion criteria are as follows: (1) no fatigue complaints or fewer than 4 symptoms; (2) severe cardiovascular, cerebrovascular, endocrine, motor, autoimmune, or infectious diseases; (3) pregnant or lactating women, drug addiction, heavy metal poisoning, or other similar conditions; (4) use of medications that may affect the judgment of the results; and (5) the participant requested withdrawal of informed consent.

### Randomization and Allocation Concealment

Patients with CFS who meet the criteria and sign the consent form will be randomized. A statistician who did not participate in the trial process will use computer software (Strategic Applications software, version 9.1.3; SAS Institute Inc) to create a random number table, which will be sent to a designated administrative staff member at the Test Management Center of Shanghai University of Traditional Chinese Medicine to ensure safety. They do not participate in the trial recruitment or treatment of participants. The administrative staff will store the patient’s identity information, treatment method, time, and location in an opaque envelope based on random numbers, before handing the sealed envelope to the research team, who will print and save it in its original form.

### Blinding

A double-blind study is difficult to implement in patients with CFS due to the difference between the 2 treatment methods. To reduce the influence of subjective factors of the patients and researchers on the study results, the Qigong and psychologists in charge of treatment will not participate in data collection, analysis, and result evaluation. Additionally, we will ensure that the evaluation and statistical analysis are performed by statistical analysts who are blinded to the grouping and intervention procedures. If the patient has an adverse reaction and requires suspension or termination of the trial, we will immediately stop the treatment and break the blind code.

### Sample Size Calculation

According to our published paper, the efficacy of the PLWNT group is assumed to be better than that of the CBT group. Referring to our previously published study [47] on the efficacy of CFS with respect to the Multidimensional Fatigue Inventory 20 (MFI-20) scale, the final difference between the 2 groups in terms of MFI-20 average scores was 1.634 and the SD was 3.238. The Bonferroni conservative comparison method was used, and the sample size of this trial was calculated using the following formula:

Considering the allowable 20% dropout rate, the sample size of each group was set at 104. Therefore, this randomized controlled trial needed to recruit 208 participants.

### Intervention

We will implement intervention measures in strict accordance with the CONSORT (Consolidated Standards of Reporting Trials) [48] and the STRICTA (Standards for Reporting Interventions in Clinical Trials of Acupuncture) [49].

#### PLWNT Group

The PLWNT intervention program and operating standards refer to the Chinese general higher TCM compiled from the college textbooks of Tuina and Qigong. Experienced Qigong teachers at Shanghai University of TCM, who have been teaching Qigong for at least 5 years, will be placed in charge of the supervision of the exercise, and they will correct participants’ exercise postures during the entire intervention period for 1 h every Sunday, including the first 10 min of each session for stretching and relaxation exercises, as well as movement introductions and demonstrations. The subsequent 20 min are allotted for individual guidance and correction of actions. Finally, all participants will practice PLWNT for 30 minutes together. For the remaining 6 days of the week, all participants will practice by themselves for 30 minutes at 6 PM o’clock every day at home, under the remote supervision of one of the directors. The practice videos will be required to be posted in a WeChat group comprising all of the study participants. If some participants find this inconvenient, videos can be sent privately to the study investigators. All participants will be asked to write down their feelings in a practice recording notebook after each exercise. The average amount of abdominal stimulation for the first 8 rubbings was 0.5 (SD 0.1) kg, and the strength of the stimulation will be monitored in real time in the LABVIEW2017 software (SHUTCM) so that the patients can feel the amount of stimulation. The entire practice process will last for 12 weeks. The content of the PLWNT Qigong intervention is the same as that reported in our previous research The 9 specific forms of manipulation are shown in Figure 2 [39,50].

**Figure 2 figure2:**
[figure not shown]
(A) Press and knead acupoint in Danzhong. (B) Rubbing from Danzhong Acupoint to Pubic Symphysis. (C) Rubbing from Pubic Symphysis to Danzhong Acupoint. (D) Pushing from Danzhong Acupoint to Pubic Symphysis. (E) The right-hand massages the abdomen by the left circle. (F) The left-hand massages the abdomen by the right circle. (G) Pushing with the right hand from the left breast to the groin. (H) Pushing with the left hand from the right breast to the groin. (I) Turn left and right. Every movement will be carried out 21 times. PLWNT: prolong life with nine turn.

#### CBT Group

Qualified CBT therapists with professionally accredited qualifications will be invited to conduct CBT for 1 h each week by giving lectures or psychological consultations on the prevention and treatment of CFS. The sessions will cover CFS diagnosis, diet and nutrition, life management, health and lifestyle changes, physical and mental health education, and medical management. On the remaining 6 days of the week, all participants will be required to listen to lectures on WeChat for 30 minutes every day. If some participants find this inconvenient, they will be allowed to learn at their own pace using the PowerPoint (Microsoft Corp) presentations provided. Each participant will be asked to write down their feelings in a practice recording notebook after each web-based session to ensure that the other conditions are the same as those of the PLWNT group. The entire practice process will last for 12 weeks. Detailed information is available in a previously published paper [39,50]; however, in this research, we will focus on CBT treatment in the gastrointestinal and nervous system fields.

### Outcome Measures

The primary outcome is the MFI-20, while secondary outcomes will include the Pittsburgh Sleep Quality Index (PSQI), Gastrointestinal Symptom Rating Scale (GSRS), Hospital Anxiety and Depression Scale (HADS), fMRI, gut microbiota, and peripheral blood. The specific study outcome assessment time points are shown in Table 1.

**Table 1 table1:** Time points of the outcomes assessment.

			Screening (T-1)^a^		Intervention								Follow up (T20)
					T0		T4	T8		T12			
Inclusion criteria			✓										
Exclusion criteria			✓										
Informed consent			✓										
Randomization					✓								
**Outcomes**													
	MFI-20^b^	✓		✓		✓		✓	✓		✓		
	SF-36^c^	✓		✓		✓		✓	✓		✓		
	PSQI^d^	✓		✓		✓		✓	✓		✓		
	GSRS^e^	✓		✓		✓		✓	✓		✓		
	HADS^f^	✓		✓		✓		✓	✓		✓		
	fMRI^g^			✓					✓				
	gut microbiota			✓					✓				
	peripheral blood			✓					✓				

^a^T0-T20: Time.

^b^MFI-20: Multidimensional Fatigue Inventory 20.

^c^SF-36: Short Form 36-item Health Survey.

^d^PSQI: Pittsburgh Sleep Quality Index.

^e^GSRS: Gastrointestinal Symptom Rating Scale.

^f^HADS: Hospital Anxiety and Depression Scale.

^g^fMRI: functional magnetic resonance imaging.

#### Primary Outcome

The MFI-20 is widely used for the measurement of mental and physical fatigue in patients with CFS [51]. It comprises 20 items, with 5 dimensions, that is, general fatigue, physical fatigue, mental fatigue, reduced activity, and reduced motivation. The total possible score is 100 points, where the higher the score, the more severe the fatigue. These will be measured at weeks 0, 4, 8, and 12.

#### Secondary Outcome

##### HADS

The HADS is used to evaluate the degree of anxiety and depression in patients. The scale consists of 14 items, including 7 items that assess anxiety and 7 items that assess depression [52]. The higher the total score, the more severe the degrees of anxiety and depression.

##### PSQI

The PSQI is a self-assessment questionnaire used to evaluate sleep quality. The scale consists of 24 items, including subjective sleep quality, sleep latency, sleep duration, habitual sleep efficiency, sleep disturbances, use of sleeping medication, and daytime dysfunction [53]. The score range for each dimension is from 0 to 3, with a total possible score of 21, where the higher the score, the poorer the sleep quality.

##### GSRS

The GSRS is mainly used to assess the severity of gastrointestinal symptoms within the past week. The GSRS includes 15 common gastrointestinal symptoms, which are divided into 5 symptom groups: reflux, abdominal pain, indigestion, diarrhea, and constipation. In addition to assessing the pain, soreness, and indigestion of the upper gastrointestinal tract, stool characteristics and discomfort of the lower gastrointestinal tract can be evaluated. Each question is scored from 1 to 7, where the higher the score, the more severe the symptoms.

##### fMRI

fMRI data will be obtained from all participants using the 3.0-T Trio Siemens System at the Shanghai Municipal Hospital of Traditional Chinese Medicine. Thirty-two head coils will be used for scanning. In the resting state BOLD signal acquisition single excitation gradient echo-plane imaging sequence, the participants will be scanned using the following parameters: repetition time (*T*_R_)=1900 milliseconds; effective echo time (*T*_E_)=2.93 milliseconds; sagittal slices=188; thickness/skip=1.2/0.6 mm; field of view (FOV)=256×256 mm^2^; matrix=240×256 mm^2^; voxel size=1.0×1.0×1.0; phase encoding direction=A>>P; and flip angle (*F*_A_)=90°. The participants will be asked to close their eyes, rest for 10 min, and not think about anything before the scan. The participants will be instructed to not move their heads during data collection. The 2 groups of participants will be tested before and after the experiment. Based on the results of previous studies, we speculated that the brain regions that may be activated include the temporal lobe, frontal lobe, and parietal lobe, which are shown in Figure 3.

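### The scan parameters listed for the resting-state BOLD sequence conflict with each other and with that sequence, so the fMRI secondary outcome is not supported if scanning follows the text

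*Protocol article*

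**What the plan says.** The fMRI section, under Secondary Outcome in the protocol article, introduces its only parameter list with these words: "In the resting state BOLD signal acquisition single excitation gradient echo-plane imaging sequence, the participants will be scanned using the following parameters". The list that follows gives:

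- repetition time 1900 ms and echo time 2.93 ms;
- "sagittal slices=188; thickness/skip=1.2/0.6 mm";
- field of view 256×256 mm and "matrix=240×256 mm";
- "voxel size=1.0×1.0×1.0", with no unit (mm assumed here);
- flip angle 90°.

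The scanner is a 3.0 T system. The article gives no other values for the BOLD scan.

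The Outcome Measures section names fMRI as a secondary outcome, and Table 1 schedules it at T0 and T12. The Statistical Analysis section first compares the amplitude of low-frequency fluctuations. It then takes the peak region as a seed and tests its connectivity with the rest of the brain. Both steps need a BOLD time series.

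**The concern.** A single-shot echo-planar BOLD scan reads a whole slice after one excitation, at an echo time long enough for T2* weighting to build up. The listed values look instead like those of a high-resolution structural scan: many thin sagittal slices, voxels near 1 mm and a very short echo time. Some of them also disagree with each other.

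What is at stake is the brain-imaging outcome. If sites scan from this text, the series would have weak BOLD weighting or could not be acquired as described, and the imaging part of the second objective (brain-gut regulation) would lose its data. Recruitment began in July 2022, so scans may already exist, and a faulty T0 scan cannot be repeated once treatment has started. If the scanner ran something else, the published specification is still wrong and nobody can verify the acquisition from it.

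**Working it through.** **Inputs from the fMRI section:** repetition time 1900 ms; echo time (TE) 2.93 ms; 188 sagittal slices; thickness 1.2 mm; skip 0.6 mm; field of view 256×256 mm; matrix 240×256; stated voxel 1.0×1.0×1.0; single excitation.

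**Assumptions not in the article:** T2* of 30 to 50 ms at 3 T; a reference TE of 30 ms; a line spacing of 0.3 to 0.5 ms in the echo-planar readout; each slice excited on its own.

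**1. Voxel size (the plan's own figure).**
- In plane, field of view divided by matrix: 256/240 = 1.07 mm and 256/256 = 1.00 mm.
- Through plane: thickness 1.2 mm, or pitch 1.2 + 0.6 = 1.8 mm.
- The stated 1.0×1.0×1.0 is not reproduced. The 1.07 could be rounding. Neither 1.2 nor 1.8 rounds to 1.0 at the precision used.

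**2. Coverage.** Slices × pitch = 188 × 1.8 = 338.4 mm, left to right because the slices are sagittal.
- Without the skip: 188 × 1.2 = 225.6 mm.
- At 1.0 mm spacing: 188 mm.
- If 0.6 were a fraction of the thickness: 188 × 1.2 × 1.6 = 361 mm.

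As written, the stack is far wider than a head. That is general knowledge; the article gives no head size.

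**3. Time per slice.** 1900/188 = 10.1 ms. Spread over 240 to 256 lines, this is 10.1 ms/240 = 42 µs to 10.1 ms/256 = 39 µs per line. At 0.3 to 0.5 ms per line, 240 lines take 72 to 120 ms, about 7 to 12 times the slot.

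**4. Echo time.** With full sampling, 120 to 128 lines precede the centre of k-space. Placing the centre at 2.93 ms needs 2.93/120 = 24 µs to 2.93/128 = 23 µs per line. At 0.5 ms per line the echo would fall at 60 to 64 ms, and at 0.3 ms at 36 to 38 ms.

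Two shortcuts were tried, neither of which the article states:
- 6/8 partial Fourier leaves 60 to 64 lines before the centre, so 49 to 46 µs per line. Adding fourfold acceleration leaves 15 to 16 lines, so 195 to 183 µs per line. Both are still shorter than 0.3 ms.
- 5/8 partial Fourier with fourfold acceleration leaves 7.5 to 8 lines. At 0.3 ms per line the echo falls at 2.25 to 2.4 ms, so 2.93 ms comes within reach. The whole readout is then 240 × 0.625/4 = 37.5 lines, or 37.5 × 0.3 = 11.3 ms, still more than the 10.1 ms slot.

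**5. BOLD weighting.** Taking contrast as proportional to TE × exp(−TE/T2*), the ratio to TE 30 ms is (2.93/30) × exp(27.07/T2*):

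| Assumed T2* | Ratio to TE 30 ms |
|---|---|
| 30 ms | 0.24 |
| 40 ms | 0.19 |
| 50 ms | 0.17 |

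**The case against.** The strongest reply is that this is a copying slip: a structural scan's parameters were printed under the BOLD label and the scanner runs a proper BOLD sequence. That may well be so. Nothing in the article shows what was actually run, so it cannot be said that scans already acquired are affected. But the list is introduced as what participants will be scanned with, so it needs correcting on either reading.

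Several stronger readings are tempting and not supported:

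- *The list cannot yield BOLD data at all.* Step 5 gives weak weighting, not none. The difficulty with the readout rests on assumed line times.
- *The 338 mm stack exceeds the 256 mm field of view.* With sagittal slices the field of view is in plane, while the stack runs perpendicular to it. The two do not limit each other, and the point is only that 338 mm is implausible for a head.
- *A 1.07 mm pixel contradicts a 1.0 mm voxel.* This may be rounding.
- *The article gives no number of volumes and no structural scan.* A condensed article can leave these to the full protocol.
- *The whole brain-gut objective fails.* The gut microbiota and blood measures do not depend on the scan settings.

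It is also fair to say that the purely internal contradiction is narrow: slice thickness or pitch against voxel size. The rest combines the article's figures with general MR physics. Slice acceleration could relax step 3, but none is stated.

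**Conclusion.** The list is wrong as a specification of the resting-state BOLD scan. From the article's own figures, a 1.2 mm slice (1.8 mm pitch) contradicts a 1.0 mm voxel. With general knowledge added, a 338 mm stack is implausible, and 10.1 ms per slice with a 2.93 ms echo does not suit a single-shot 240×256 readout at ordinary line times. BOLD weighting would be roughly 17-24% of that at 30 ms, for T2* of 50 to 30 ms.

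If scanning followed the text, the fluctuation and connectivity analyses, and with them the fMRI secondary outcome, would not be supported. Whether it did is unknown. The MFI-20 analysis and the sample size of 208 are untouched, so the correction is needed for the imaging outcome and not for the trial as a whole.

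**What to change.** 1. Compare the list with the scanner protocol actually in use.
2. Replace it with the true resting-state echo-planar values: repetition time, echo time, slices, thickness and gap, matrix, voxel size with unit, flip angle and number of volumes. If the present values belong to a structural scan, move them under that label.
3. Check the exported headers of scans acquired since July 2022.
4. Only if that check shows that some participants have no valid BOLD series, restrict the fMRI outcome to those who have one, and state this with the numbers per arm.

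The cost is a text correction and one pass through the scan headers. No change to the primary analysis or the recruitment target is needed.
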